### Sample size

The primary endpoints are group differences in self-reported knee function measured using the KOOS-ADL at 3 and 6 months using mixed-effect linear regression. The KOOS-ADL score ranges from 0 to 100 with higher scores indicating better function. We aim to detect a difference of at least 7 points,^16^ and a common SD of 15 points was assumed. The sample size was estimated assuming two-sided, two-sample equal-variance t-test, with an overall type I error rate (α) of 0.05. The effect size is defined as d=(μ1−μ2)/σ, where σ is the common SD for both groups. To detect a population effect size of 0.40 with 85% marginal power, the number of needed participants will be around 150 in each group after adjusting for 10% loss to follow-up and multiplicity due to two primary time points using Bonferroni’s correction. The sample size was computed using PASS 2023, V.23.0.2. We expect to reach the target sample size in 18 months.

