### Outcomes

Primary outcome: Early recovery of knee function is one of the desired outcomes by patients undergoing knee arthroplasty.^14^ The primary outcome knee function will be assessed using the ADL subdomain of Knee Injury and Osteoarthritis Outcome Score (KOOS). It is a validated tool to evaluate post knee rehabilitation interventions^15^ and will be completed by the trial participants at baseline (before surgery status), 3 and 6 months after surgery in both groups. The total score ranges between 0 and 100 and the minimum clinically important group difference for this domain ranges from −1.5 to 15.5 units.^16^ The KOOS-ADL questionnaire will be self-administered in paper during the follow-up visit by the patient. If the patient is not able to complete it by self, then the family member will assist in eliciting the responses from the patient. In the absence of a family member, an independent assessor, not involved in the intervention implementation and rehabilitation, will administer the questionnaire. The primary comparisons would be to compare the end value of KOOS-ADL score at 3 and 6 months independently between the two groups adjusted for baseline score.

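### The stated 7 points and SD of 15 give an effect size of 0.47, but the trial is sized for 0.40, so difference, SD and 85% power do not fit together; the mismatch is conservative

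*Protocol article*

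**What the plan says.** All the planning figures stand in one paragraph of the protocol article, under Sample size.

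- Difference and SD: "We aim to detect a difference of at least 7 points,^16^ and a common SD of 15 points was assumed".
- Definition: "The effect size is defined as d=(μ1−μ2)/σ, where σ is the common SD for both groups".
- Test: "The sample size was estimated assuming two-sided, two-sample equal-variance t-test", with an overall type I error rate of 0.05.
- Sizing: "To detect a population effect size of 0.40 with 85% marginal power". The result is around 150 per group after allowing for 10% loss to follow-up and a Bonferroni correction for two primary time points.

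The section Statistical methods for primary and secondary outcomes confirms a significance level of 0.025 at each time point. The abstract gives the total as 300. Nothing in the article explains how 0.40 relates to the 7 points and the SD of 15.

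**The concern.** The paragraph supplies both the formula and its two inputs, and the formula does not return the effect size used two sentences later. Nothing is missing here that an SAP would normally add. The difference, SD, definition, effect size, alpha, power, loss and sample size are all printed, and they disagree.

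What is at stake is the stated basis of the trial. A reader cannot tell whether it was built for 6 or 7 points, on an SD of 15 or 17.5, or with 85% or about 94% power per time point. Trial reports usually repeat this paragraph, so the ambiguity would carry into the results paper. A choice among these readings is credible only if it is made before results are known.

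**Working it through.** **Inputs.** From Sample size: difference 7, SD 15, d = difference/SD, d used = 0.40, power 85% per time point, two-sided two-sample t-test, overall alpha 0.05 split over two time points, 10% loss, around 150 per group. From Statistical methods: alpha 0.025 per time point. From Assignment of interventions: 1:1 allocation.

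**Step 1. Effect size from the stated inputs.** d = 7/15 = 0.467. Rounding does not turn this into 0.40. Working back from 0.40: 0.40 × 15 = 6.0 points, or 7/0.40 = an SD of 17.5.

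**Step 2. Reproduce the plan's figure with d = 0.40.** The normal approximation is n per group = 2(z₁ + z₂)²/d², with z₁ = 2.241 (two-sided 0.025) and z₂ = 1.036 (85% power). The numerator is 2 × 3.278² ≈ 21.49.

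- Normal approximation: 21.49/0.16 = 134.3, so 135 per group; 135/0.9 = 150.
- Exact noncentral t: 136 per group; 136/0.9 = 151.1, rounded up to 152. Multiplying by 1.1 instead gives 149.6, rounded up to 150.

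The stated figure of around 150 therefore reproduces.

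**Step 3. The same calculation with d = 7/15.**

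- Normal approximation: 21.49/0.2178 = 98.7, so 99 per group; 99/0.9 = 110.
- Exact t: 100 per group; 100/0.9 = 111.1, so 111 to 112 randomised, or 222 to 224 in total against the planned 300.

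**Step 4. Power with 150 randomised per group.** After 10% loss, 150 × 0.9 = 135 are evaluable per group. At two-sided alpha 0.025:

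| Effect size | Normal approximation | Exact t |
|---|---|---|
| 0.40 | 85.2% | 84.8% |
| 0.467 | 94.4% | 94.2% |

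With 135 evaluable per group and SD 15, the difference detectable with 85% power is 6.0 points.

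**Step 5. Could another reading of 7 and 15 give 150?** With d = 7/15, alpha of 0.05 or 0.025, power of 80%, 85% or 90%, and either way of inflating for loss, the largest result is 129 per group (alpha 0.025, 90% power, exact t 116, and 116/0.9 = 128.9). None reaches 150.

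**The case against.** The strongest reply is that the operative number is sound. The protocol names 0.40 as the effect size for which it sizes the trial, and 150 per group is right for that value. If 7 points and SD 15 are true, the trial has more power than claimed. Randomisation, test, estimand and error control are untouched. All of this stands, and it limits the weight of the point. A deliberately cautious effect size, or a larger SD, might explain the 0.40. The article states neither and gives the SD as 15. The words at least before 7 points do not help, because a larger difference moves d further from 0.40.

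A second fair reply is that 85% and 94% describe an unadjusted t-test, whereas the planned mixed model adjusts for the baseline score. Neither figure is the power of the actual analysis. They are comparable with each other and with the plan's own calculation, which is all this point needs.

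Three stronger readings are tempting, and the documents do not support them.

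- *The trial is underpowered.* The error runs the other way.
- *One particular figure is wrong.* The figures are mutually inconsistent, but nothing shows whether the difference, the SD or the power is the one to change. The SD of 17.5 is a back-calculation and appears nowhere in the article.
- *The quoted range for clinical importance makes matters worse.* The Outcomes section says "the minimum clinically important group difference for this domain ranges from −1.5 to 15.5 units". A reader might note that this range includes zero, that 7 is its midpoint, and infer that almost any result could be called important. However, the article only reports the range from a reference that is not at hand. It does not say that 7 was derived from it, and it names a single positive target. Neither the range nor the 7 points is a decision rule: the primary comparison rests on mean differences with 95% confidence intervals and a p value threshold of 0.025.

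**Conclusion.** The point holds as an internal inconsistency. By the protocol's own definition, the stated difference and SD give d = 0.47, while the sample size rests on d = 0.40. At 150 per group, 7 points, SD 15 and 85% marginal power cannot all be true.

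The gap is about 9 percentage points of power per time point (94.2% against 84.8%). Put as sample size, it is about 100 against 136 evaluable per group. This rests on a two-sided equal-variance t-test at alpha 0.025 and 10% loss, as the protocol states, without credit for baseline adjustment.

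Because the inconsistency is conservative and enrolment is unaffected, it is a minor point, or at most one that should be fixed. It does not threaten the trial's validity.

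**What to change.** Keep the total at 300 and restate the basis as one consistent set:

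- 6 points, SD 15, d = 0.40, 85% marginal power; or
- 7 points, SD 17.5, d = 0.40, 85% marginal power; or
- 7 points, SD 15, d = 0.47, about 94% marginal power.

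The authors know which they intended and should say so, with a sentence of justification if 0.40 was chosen as a cautious value. The restatement belongs in the protocol and in the SAP, which the protocol promises before recruitment ends and will make public before the final analysis. It should be settled before any analysis.

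The cost is one paragraph. Enrolment, outcomes, eligibility and follow-up do not change, so none of the amendment types that the Trial management section sends for ethics approval is triggered.

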### Data collection and management

Data will be collected at the physiotherapy clinic of the recruiting hospitals in paper forms at baseline and at 3 and 6 months postrandomisation by a trained research coordinator. Data will be single entered into a web-based electronic data capture system (REDCap) with in-built validation checks and a query management system. Source data verification will be done by the trial manager to check for accuracy against the paper forms. Initially, 100% of forms will be checked and the subsequent percentage of the forms checked will depend on the proportion of transcription errors identified. Data related to cost will be entered into an excel sheet for further processing.

To ensure data quality, periodic data review checks will be done by the trial manager not involved in data collection, using Stata to flag discrepancies that may not be detectable by inbuilt automatic checks. These checks include cross-form logic checks and completeness of critical fields. Queries will be raised in REDCap for the research coordinator to update or respond. A back-up of all data will be done periodically as per the institution server policy. The paper forms, along with informed consent, will be safely secured in a cabinet with restricted access at the Sponsor institute.

Semistructured interviews will be conducted either face-to-face or telephonically from a purposively selected sample of trial participants based on the extent of app usage (users, partial-users, non-users). The interviews will be audio-recorded or written notes will be taken depending on how comfortable the participants are with the audio recording. Participants will be invited for interviews until data saturation is reached. All the healthcare providers involved in the intervention implementation at the hospital will be interviewed. The interviews will be conducted by a member of the research team trained in qualitative interview methods. Qualitative interviews will be transcribed and translated by one of the members of the research team and cross-checked by another member of the team for correctness and appropriateness.

### Participant retention strategies

The research coordinator involved in recruitment will telephonically contact the trial participants of both groups at least once a month for rapport building and to enquire about their health. For the app group participants, any technical query related to the app will also be resolved. Travel reimbursements will be provided to trial participants at 3-month and 6-month visits, as per the clinical site ethics committee’s recommendation. We will share a newsletter in English and Hindi every 2 months with all trial participants to provide an update on trial progress and encourage them to visit the hospital for their trial related follow-up. If a participant is unable to make it to the hospital for a follow-up visit, participant reported outcome measures will be collected telephonically and the participant will be motivated to visit the hospital at the earliest for conducting the performance-based measurements.

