#### App-based rehabilitation

The overarching goal of the intervention is to aid recovery, provide opportunities for the physicians to provide continuity of care and to reduce out-of-pocket expenses associated with the rehabilitation phase. The intervention has five interlinked components with defined functions and will be delivered via the TReAT app (figure 2, online supplemental efigure 1). The details of the stages of the intervention development have been published elsewhere. The intervention has the following components and functions:

Education to impart knowledge: A digital and a printed booklet with 12 chapters, consisting of context specific information related to preparing oneself for surgery, knowing about recovery process and important do’s and don’ts to safeguard the new knee, in English and Hindi will be made available at the time of enrolment (online supplemental efigure 2).

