Secondary outcomes: Other quantitative outcomes include pain, assessed using the nine-item KOOS-Pain questionnaire^15^ with a 5-point ordinal response scale, higher scores indicating higher levels of pain. Activity level will be assessed using the lower extremity activity scale,^17^ a single item self-reported question with 18 states of activity, higher numbers indicating higher level of activity. Quality of life will be assessed using the EuroQoL-5 Dimensions-5 Levels questionnaire,^18^ capturing five domains of health, namely mobility, self-care, usual activities, pain/discomfort and anxiety/depression. The overall score ranges from 0 to 1, higher score indicating better quality of life. Safety, knowledge about recovery, rehabilitation adherence, satisfaction with surgical outcome and cost incurred will be collected using study-specific questionnaires. Active and passive knee ROM^19^ of the operated knee(s) will be measured using a digital goniometer. Performance-based measurements include chair rising test to assess lower limb strength, stair climbing and 6 min walk tests to assess knee function, timed-up and go to assess gait stability,^20^ and single leg stance to assess balance.^21^ Further explanation of the measurement tools is found in table 2 and the standardised procedure to conduct the performance-based tests is illustrated in online supplemental efigure 8.

**Table 2 T2:** Trial outcomes and schedule of data collection

	Study period					
Time point	Enrolment	Baseline (0)		Visit 1 (3 months)		Visit 2 (6 months)
Screening	X		Telephonic health check-in		Telephonic health check-in	
Informed consent	X					
Health history (comorbidities)		X				
Randomisation	X					
Patient-reported outcome measures						
Knee function*		X		X		X
Knee pain†		X		X		X
Activity level‡		X		X		X
Quality of life§		X		X		X
Knee range of motion¶		X		X		X
Safety** (falls and rehospitalisation)				X		X
Knowledge about recovery††				X		
Rehabilitation adherence‡‡				X		
Cost incurred by patients§§				X		X
Satisfaction with surgical outcome¶¶						X
Performance based measures*** Function (SCT, 6MWT), Gait stability (TUG), Lower limb strength (CRT), Balance (SLS)				X		X
Process indicators††† Implementation fidelity and reach of the intervention, app usage, barriers and facilitators to implementation and end user satisfaction.						

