* Knee function assessed using the Activities of Daily Living subdomain of KOOS, a self-reported 17-item questionnaire with 5-point ordinal scale responses, with score ranging from 0 to 100, higher score indicating better knee function.

† Knee pain will be assessed using the pain subdomain of KOOS (9 items) with 5-point ordinal scale responses. Score ranging from 0 to 100, higher score indicating severity of pain.

‡ Activity level assessed using lower extremity activity scale a single item question with 18 states of activity levels, higher level indicating higher activity.

§ Quality of life assessed using EQ-5D-5L, a 5-item questionnaire capturing 5 domains-mobility, self-care, usual activities, pain/discomfort, and anxiety/depression. The score ranges from 0 to 1, higher score indicating better quality of life. Additional Visual Analogue Scale for rating current state of health (0–100).

¶ Knee range of motion-active and passive flexion and extension of operated knee(s) using digital goniometer in supine position.

** Safety—number of falls after discharge to home as reported by the family or patient and number of rehospitalisations due to index knee surgery.

†† Knowledge about recovery-14 item studyp-specific questionnaire.

‡‡ Rehabilitation adherence-22-item study-specific questionnaire.

§§ Cost incurred by the patient after surgery for physiotherapy services and medications, travel, re-hospitalisation and potential productivity loss.

¶¶ Satisfaction with surgical outcome—8-item Likert scale questionnaire.

*** Performance based measures—SCT measured as time in seconds to complete climbing up and down 12 steps of 18 cm in vertical height; 6 minute walk testT-Distance covered in 6 min at self-paced walking; TUG- Time (in secs) taken to rise from a chair of 44 cm height, walk for 3 m, turn back and be seated on the same chair. CRT-number of repetitions in 30 s to raise rising chair of 44 cm height; SLS—time in seconds an individual can stand on a single leg with eyes open.

††† Process indicators will be assessed by triangulating the findings from the screening logs, research coordinator observations, app analytics data and qualitative interviews with the end users.

CRT, chair rising test; EQ-5D-5L, EuroQol-5 Dimensions-5 Levels; KOOS, Knee Injury and Osteoarthritis Outcome Score; 6MWT, 6 Minute Walk Test; SCT, stair climbing test; SLS, single leg stance; TUG, Timed Up and Go.

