### Statistical methods

#### Statistical methods for primary and secondary outcomes

Effectiveness outcomes: Baseline characteristics including mean, SD, number and percentage will be described. Mean group differences and 95% CI of KOOS-ADL score at 3 and 6 months adjusted for baseline score will be calculated using mixed effect linear regression. A p value of 0.025 will be considered as statistically significant for each of the time points. The analytical approach will be modified intention-to-treat, which includes all those who were randomised irrespective of their adherence to trial protocol if they had at least one follow-up visit after enrolment. This approach will exclude those who were lost to follow-up after enrolment.

All secondary continuous outcomes that include KOOS-Pain, ROM and performance-based measures will be compared at 3 and 6 months using linear mixed effect method adjusted for baseline KOOS-ADL, as performance-based measures will not be collected at baseline. A statistical analysis plan will be developed before the end of trial recruitment and made publicly available before final analysis. No interim analysis will be performed. The preplanned subgroups are gender and laterality of index surgery (bilateral/unilateral). Effect modification will be claimed based on interaction p<0.05. We will not perform a per-protocol analysis. Multiple imputation of missing primary outcome will be done only if more than 5% of enrolled are lost to follow-up. All analyses will be done in Stata (StataCorp) and R version 4.4.1 or higher (Postit Team, 2025).

Process evaluation: App usage (usage of diary, type of exercise prescribed and number of times therapy was modified) will be presented graphically along with suitable summary measures. The written research coordinators’ notes will be quantified using a fidelity checklist. Transcripts of qualitative interviews will be coded independently in NVivo software (Lumivero (2023) NVivo (V.14)), using an inductive-deductive approach followed by thematic analysis. The qualitative findings from the interviews, fidelity checklist, rehabilitation adherence and knowledge score, and functional outcomes will be triangulated to understand the mechanistic pathway to change, whether intervention use/non-use led to different outcomes. Further, contextual factors affecting the implementation and usage of the intervention will be summarised.

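### Phone-only follow-up leaves range of motion and performance tests missing, and the stated model corrects for this only partly if attendance depends on current function and differs by arm

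*Protocol article*

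**What the plan says.** Participant retention strategies sets two routes for a missed visit, one for questionnaires and one for tests: the patient-reported "outcome measures will be collected telephonically and the participant will be motivated to visit the hospital at the earliest for conducting the performance-based measurements". ROM cannot be taken by phone either: the Outcomes section says that ROM "of the operated knee(s) will be measured using a digital goniometer", and the notes to Table 2 specify the supine position. The retention section does not name ROM in the catch-up.

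Statistical methods for primary and secondary outcomes says that the continuous secondary outcomes, including ROM and the performance measures, "will be compared at 3 and 6 months using linear mixed effect method adjusted for baseline KOOS-ADL". On missing data it says: "Multiple imputation of missing primary outcome will be done only if more than 5% of enrolled are lost to follow-up". A statistical analysis plan is promised before the end of recruitment.

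**The concern.** The protocol foresees a specific missing-data pattern: questionnaires present, physical tests absent, at the same visit. It then names an analysis for the tests that leaves out the best information on how the absent patients are doing, namely their KOOS-ADL, KOOS-Pain and activity scores at that visit. (KOOS-Pain falls under the same model, but it can be taken by phone and is not affected.)

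This matters for the group comparison only if non-attendance depends on current function and differs between arms in rate or reason. That is possible here. The trial is open-label, the introduction reports that patients found hospital travel hard, and the app offers remote consultation and aims "to reduce out-of-pocket expenses associated with the rehabilitation phase". App patients who are recovering well might see little need to travel, while usual-care patients who are recovering poorly might be unable to.

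The affected outcomes are secondary. They are, however, the assessor-measured outcomes in a trial whose primary outcome is reported by unblinded patients, so they are a natural check on it. Knee flexion also enters the planned cost per 5° gained.

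**Working it through.** **The plan's own figure.** None is given for this point. The sample size section supplies a yardstick: standardised effect 0.40, 85% power, significance level 0.025 per time point, 10% loss. n = 2(2.241 + 1.036)²/0.40² = 134.3, so 135 per arm, and 135/0.90 = 150, as stated. That figure concerns KOOS-ADL and is not in dispute.

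**What the stated model uses.** For a participant with no 6-month test, it can draw on arm, baseline KOOS-ADL and the 3-month test if there was one. It does not use 6-month KOOS-ADL. If absence depends on 6-month function, part of that dependence is left uncorrected.

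**Size.** A large-sample simulation (300,000 per arm, no true effect) generated KOOS-ADL at 0, 3 and 6 months and a standardised test score (higher is better) at 3 and 6 months. The following inputs are assumptions, not taken from the protocol:

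- correlation of same-visit KOOS-ADL and test: 0.6
- correlation between visits: 0.6
- correlation of baseline KOOS-ADL with later KOOS-ADL: 0.4, and with the test: 0.3
- log-odds of absence: 0.8 per SD of current KOOS-ADL

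Three estimates of the 6-month difference (app minus usual care, in SD) were compared: observed tests only; the stated model, by maximum likelihood on baseline KOOS-ADL and both test visits; and the same likelihood with 3- and 6-month KOOS-ADL added.

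| Phone-only, app / usual care | Who stays away | Observed only | Stated model | With follow-up KOOS-ADL |
|---|---|---|---|---|
| 10% / 10% | poor function, both arms | 0.00 | 0.00 | 0.00 |
| 20% / 20% | poor function, both arms | 0.00 | 0.00 | 0.00 |
| 20% / 10% | poor function, both arms | +0.044 | +0.031 | 0.00 |
| 10% / 10% | app: good; usual care: poor | −0.089 | −0.055 | 0.00 |
| 15% / 15% | app: good; usual care: poor | −0.132 | −0.086 | 0.00 |
| 20% / 20% | app: good; usual care: poor | −0.172 | −0.114 | 0.00 |

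In the rows with bias, the stated model removes 30% to 38% of the observed-only bias (for example 1 − 0.031/0.044 = 30% and 1 − 0.055/0.089 = 38%).

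**Against the yardsticks.** 0.031/0.40 = 8% and 0.114/0.40 = 29% of the effect used for the primary sample size. With 120 tested per arm, the unadjusted standard error is √(2/120) = 0.129 SD, so 0.114 SD is about 0.9 of a standard error.

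**Sensitivity.** With log-odds 1 per SD and a same-visit correlation of 0.5 or 0.7, the stated model gives 0.034 or 0.048 SD in size for 20% against 10% with the same reason. For 20% in each arm with opposite reasons it gives 0.125 or 0.178. The upper end therefore moves with the assumptions; the zero under equal rates and reasons does not.

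**The case against.** The strongest reply is that missing-data handling for secondary outcomes, and the choice of auxiliary variables, normally sit in the statistical analysis plan, which is promised and not shown. The imputation sentence can also be read as setting a trigger for the primary outcome without ruling out imputation elsewhere. This stands in part. It makes the point an improvement to a stated method, not an error. But the article does name the model, its covariate and the scope of imputation, and as named they do not fit the pattern that the retention section creates.

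A reader might infer that the tests are compared only among those who travel on schedule, with no correction. The documents do not support that. Catch-up visits are sought, the mixed model keeps anyone tested at either visit, and it corrects fully if absence depends only on baseline KOOS-ADL and the other visit's value.

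The size rests on assumed inputs. The larger values need opposite reasons for absence in the two arms and 15–20% per arm never tested even after catch-up. Several measures limit this: people unable to attend at 3 and 6 months are excluded, travel is reimbursed, and both arms get monthly calls and newsletters. All of this stands. So does the caution that the perfect correction in the last column is built in, because absence was simulated to depend on the score that is then used.

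It is also tempting to say that tests done late should be discarded, since the catch-up has no stated time limit. Replacing real assessor-measured values with predictions from self-report is a debatable trade, and no calculation here shows that late tests cause bias.

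**Conclusion.** The point holds in a limited form. Phone-only visits are planned for, and the named analysis of ROM and performance tests uses only part of the information available for those patients. Under assumed phone-only shares of 10–20% per arm, the spurious difference ranges from about 0.03 SD (unequal rates, same reason) to about 0.11 SD (opposite reasons), and is zero when rates and reasons are equal. Stronger assumed dependence gives larger values.

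A reader might conclude that these outcomes will be biased, or biased in favour of one arm. Neither follows: the documents do not establish that attendance will differ by arm, and the sign changes between scenarios. The primary comparison is not touched by this gap, because KOOS-ADL can be taken by phone. The change is worth making because it is cheap and uses data already collected.

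**What to change.** In the analysis plan, for ROM and the performance measures:

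- Use multiple imputation or a joint mixed model that includes the same-visit KOOS-ADL, KOOS-Pain and activity scores, whether taken by phone or in clinic, together with arm, site and baseline KOOS-ADL.
- Report in-person attendance by arm and visit, so that readers can judge whether the condition for bias arose.
- Keep late catch-up tests in the main analysis with their actual dates recorded. Restrict to tests within a window set before outcome data are seen only as a sensitivity analysis.

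No new data are needed beyond recording the mode of contact and the test date. The cost is a little extra analysis and one further assumption: the imputation model is learned largely from patients who completed the questionnaire on paper in clinic, so phone scores must be comparable with paper scores. Participants who give scores by phone and later come in for tests offer a partial check. Correction is complete only if attendance depends on the scores that are included.
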